### Economic outcomes

For the economic evaluation we will make use of the pertinent guidelines [36,41-43]. The societal perspective will be taken encompassing intervention costs, direct non-medical costs and indirect costs. The latter is not expected to be very important in the studied population, which is characterised by unemployment, but the data on production losses will be collected anyway. Production losses will be economically valuated using the friction cost method [44]. Costs and effects will be analysed simultaneously, incremental cost-effectiveness ratios (ICERs) will be calculated and placed within 95% confidence intervals, 2,500 bootstrap replications of the ICERs will be projected on a cost-effectiveness plane, ICER acceptability curves will be plotted against different willingness-to-pay ceilings [45], and sensitivity analysis will be conducted as a matter of course focussing on uncertainty in the main cost-drivers. This will be done for the costs per QALY gained in a cost utility analysis.

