### Sample size

Based on a priori power analyses for hierarchical multiple regression, assuming a power of .80, Cohen’s d of .80 and alpha of .05, each study condition will need at least 43 cancer survivors. We will anticipate for loss to follow-up of 30%, and will therefore need 56 cancer survivors per condition at baseline. In total, we will recruit 168 cancer survivors during an inclusion period of 2.5 years.

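### A 95% confidence interval is planned on the ICER without condition; it becomes uninterpretable or unbounded if the QALY difference is not clearly away from zero

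*Protocol article*

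**What the plan says.** The Economic outcomes section of the protocol article plans a cost-utility analysis. Its ratio is fixed by the closing sentence: "This will be done for the costs per QALY gained in a cost utility analysis". On uncertainty it commits to four things:

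- an interval on the ratio, with the bootstrap named directly after it: "incremental cost-effectiveness ratios (ICERs) will be calculated and placed within 95% confidence intervals, 2,500 bootstrap replications of the ICERs";
- a bootstrap display: "2,500 bootstrap replications of the ICERs will be projected on a cost-effectiveness plane";
- acceptability curves: "ICER acceptability curves will be plotted against different willingness-to-pay ceilings";
- a sensitivity analysis of the main cost drivers.

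It adds "Costs and effects will be analysed simultaneously". It does not say how the ICER interval will be built. It gives no rule for replicates in which the QALY difference is zero or negative, and it does not make the interval conditional on the QALY result. No expected QALY difference, cost difference or standard deviation appears anywhere in the article. The Sample size section says the trial "will therefore need 56 cancer survivors per condition at baseline" and allows for 30% loss.

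**The concern.** The ICER is the cost difference divided by the QALY difference, so its sign does not identify the conclusion. A negative value arises when the new treatment is cheaper and better, and also when it is dearer and worse. A positive value arises when it is dearer and better, and also when it is cheaper and worse. Once the sampling distribution of the QALY difference straddles zero, sorting the ratios from low to high no longer sorts them from favourable to unfavourable.

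The Background section makes cost-effectiveness part of the main goal, against both supportive group therapy and usual care. One of these comparators is itself an eight-session group therapy. In addition, the intervention targets meaning, while QALYs come from the EQ-5D. A small QALY difference is therefore a realistic possibility. An ICER with an interval is easily lifted from a paper and set against a threshold, and in that situation the comparison would not be informative.

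**Working it through.** The plan has no economic figure to reproduce, so the check asks when an interval on the ratio can be read.

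**Inputs from the article:** 56 per arm at baseline; 30% loss, leaving 56 × 0.70 = 39.2, about 39; 2,500 replicates.

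**Assumptions, not in the article:** QALY SD 0.15 to 0.25; QALY gain 0 to 0.10; for the illustration, cost difference 800 euro, cost SD 5,000 euro, QALY SD 0.20, independent normal differences. Clustering is ignored throughout.

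**1. When a Fieller interval is bounded.** It has finite limits only if the observed QALY difference exceeds 1.96 SE, with SE = SD × √(2/n). In SD units no SD need be assumed:
- n = 56: 1.96 × √(2/56) = 0.37 SD
- n = 39: 1.96 × √(2/39) = 0.44 SD

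For SD 0.15 to 0.25 this is 0.056 to 0.093 QALY with 56 per arm, and 0.067 to 0.111 with 39. Participants are randomised in groups of 8 (56/8 = 7 groups per arm), and positive correlation within groups would raise these thresholds.

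**2. Share of replicates below zero QALY difference.** Replicates centre on the observed difference dQ, so the share is Φ(−dQ/SE). For example, with SD 0.20 and n = 56, SE = 0.20 × √(2/56) = 0.0378 and Φ(−0.02/0.0378) = 0.298. Over SD 0.15 to 0.25:

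| dQ | 56 per arm | 39 per arm |
|---|---|---|
| 0 | 50% | 50% |
| 0.02 | 24–34% | 28–36% |
| 0.05 | 4–15% | 7–19% |
| 0.10 | at most 2% | at most 4% |

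**3. What percentile limits look like** (2,500 simulated replicates, 56 per arm; quadrants are dearer/better, cheaper/better, dearer/worse, cheaper/worse):

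| dQ | Point ICER | Percentile limits | Quadrant shares (%) |
|---|---|---|---|
| 0.02 | 800/0.02 = 40,000 | −435,113 to 372,201 | 55 / 15 / 23 / 7 |
| 0.05 | 800/0.05 = 16,000 | −147,175 to 168,809 | 71 / 20 / 8 / 1 |
| 0.10 | 800/0.10 = 8,000 | −12,085 to 43,607 | 80 / 20 / 0.1 / 0 |

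At 0.02 the negative ratios come from 15% of replicates that favour the intervention and 23% that count against it, so the lower limit has no single meaning. At 0.10 the negative part reflects almost only dominance, and the interval can be read. The euro values follow from the assumed costs and are an illustration only.

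**4. The alternative in the same difficult case.** Incremental net monetary benefit at ceiling λ is λ·dQ − dC, with SE = √[(λ·SE_Q)² + SE_C²] under independence. With dQ = 0.02, SE_Q = 0.0378 and SE_C = 5,000 × √(2/56) = 945:
- λ = 20,000: 400 − 800 = −400; SE = √(756² + 945²) = 1,210; 95% interval −400 ± 2,372, or −2,772 to 1,972
- λ = 50,000: 1,000 − 800 = 200; SE = √(1,890² + 945²) = 2,113; 95% interval 200 ± 4,141, or −3,941 to 4,341

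These intervals are wide, but they are finite and ordered from unfavourable to favourable. The simulated probabilities of being cost-effective at these ceilings, 0.38 and 0.55, are equally well defined.

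**The case against.** The strongest reply is that the article never says percentile. A reader might infer it from the bootstrap named in the same sentence, but the text does not support treating it as stated, and the construction may be settled in a fuller document. That stands. It does not remove the point, because the Fieller construction has its own condition (step 1), and the article commits to the interval without one.

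A reader might also infer that all the reported economic uncertainty would be meaningless. The documents do not support this. The plane and the acceptability curves, planned in the same sentence, show the joint uncertainty correctly whatever the sign of the QALY difference. The article attaches no test or decision rule to the ICER interval.

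Nor do the documents show that a near-zero QALY difference is to be expected. They contain no QALY figure, and at a gain of 0.10 the difficulty largely disappears. The Sample size section assumes a standardised effect of 0.80; were that the QALY effect, the threshold of 0.37 SD would be passed easily. However, the section does not apply it to QALYs.

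Coverage is not the failure either. In the simulation, percentile intervals covered the true ratio in 94 to 98% of runs for QALY differences of 0.01 to 0.15. The fault lies in what the limits mean, not in how often they contain the number.

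Finally, resampling by whole groups or ordering all three arms in one incremental analysis does not follow from the ratio problem and is not part of this point.

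**Conclusion.** The point holds in a limited form. The article plans an interval on the ICER itself without condition, and that interval can be read only when the QALY difference is clearly away from zero. For a bounded Fieller interval, clearly means above about 0.37 SD with 56 per arm or 0.44 SD with 39, and somewhat more if outcomes correlate within therapy groups. Whether the trial falls short of this depends on an effect size that the article does not give. Under the assumed SDs it is a real risk at gains of 0.02 to 0.05 and a minor one at 0.10. The damage is confined to one of several planned presentations of uncertainty. The change is still worth making, because the alternative is interpretable in every case and almost free.

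**What to change.** In the Economic outcomes section, report the ICER as a point estimate. Give 95% intervals, from the 2,500 replicates already planned, for incremental costs, incremental QALYs, and incremental net monetary benefit at the willingness-to-pay ceilings chosen for the acceptability curves. Keep the plane, the curves and the sensitivity analysis as they are.

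The cost is a change of wording plus a simple calculation on existing bootstrap output; no further data or resampling are needed. The small downside is that readers who look for an interval on the ICER will not find one, so one sentence should say why and point them to the net-benefit intervals.

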### Ethical considerations

This study is conducted in accordance with local laws and regulations. Eligible patients are fully informed about the study and asked to participate. The patients receive a patient information sheet and flyer and they are also informed by telephone about the implications of participation. Patients have ample opportunity to ask questions and to consider the implications of the study before deciding to participate. Patients provide written informed consent, compliant with the local and ethical regulations, before participation. Patients are allowed to withdraw from the study without giving a reason, at any time. The study protocol has been approved by the Medical Ethical Committee of Leiden University Medical Center, Leiden, The Netherlands.

## Discussion

The proposed study will assess the effectiveness of MCGP-CS, compared to SGP and to CAU in cancer survivors with psychological or existential distress after treatment. In addition, the cost-effectiveness of MCGP-CS will be determined.

There is a growing need for psychological interventions that target the issues that cancer survivors are dealing with in the aftermath of their disease. Meaning-focused coping is key to adjustment to life after cancer [7,46]. Many cancer survivors experience feelings of loneliness and alienation, and have a need for peer support, therefore a group method in particular, can be beneficial [47]. Group interventions may provide opportunities to cope with these problems. People who benefit from group interventions feel more comforted, less alone and have learned different ways to cope with their situation [47].

To our knowledge there are no RCT’s that evaluate the effectiveness of meaning-centered psychotherapy for cancer survivors. Also, there is little known about who benefits from these types of interventions. Also, there is little known on who benefits from these types of interventions. We want to conduct an RCT that compares MCGP-CS with a SGP that focuses on other issues that cancer survivors deal with (see Table 2). This way, we hope to establish whether a meaning-centered approach is more effective compared to care as usual, than a non-meaning-centered approach. Secondary analyses will be conducted to assess the predictors of effectiveness on an individual level, in order to gain more knowledge on which people benefit the most from the meaning-centered intervention.

To our knowledge, there are no cost evaluations of meaning-centered interventions. Since the number of cancer survivors is increasing rapidly, cost efficient psychological care is, from an economic point of view, important to warrant the feasibility of implementation in mental health care settings.

This study evaluates if MCGP-CS is effective for cancer survivors and if so, whether this is a cost efficient method. If this MCGP-CS is effective for cancer survivors, it can be implemented in the practice of psycho-oncology care. The broad collaboration in this project with several hospitals and psycho-oncology organisations, facilitates possible implementation in practice after this evaluation. There are few evidence based group intervention manuals available for cancer patients. For meaning-centered group psychotherapy for cancer survivors, there are no evidence based intervention manuals yet. Therefore, if the results of this RCT are positive on effectiveness measures, the intervention protocol can be an important addition to the advancement of evidence based psychological care for cancer patients.
